## Abstract

**Background:**

High salt intake is a risk factor for hypertension and cardiovascular disease. Reducing salt intake has been shown to reduce blood pressure. Despite population-level interventions, including product reformulation and public awareness campaigns, adult salt consumption in the UK still exceeds recommendations; this is primarily due to salt consumed in processed and pre-packaged foods. Moderate or high-intensity dietary advice to encourage individuals to reduce their salt intake has been shown to be effective at reducing blood pressure, but evidence of the effectiveness of interventions that are suitable for delivery at scale in routine primary care is scarce. This feasibility trial investigates a complex behavioural change intervention to reduce dietary salt intake and blood pressure by encouraging individuals to purchase lower-salt foods when grocery shopping.

**Methods:**

This randomised controlled trial will test the feasibility of a novel intervention to reduce salt intake, and the trial procedures to assess its effectiveness. We will recruit participants through UK general practices and randomise 40 participants with high blood pressure, in a 2:1 allocation to receive either the Salt Swap intervention or a control information leaflet. The primary outcomes relate to the criteria for progression to a large-scale trial. These include follow-up rates at 6 weeks, fidelity of intervention delivery and use of the intervention mobile app. Secondary outcomes include the effect of the intervention on the salt content of purchased foods (grams per 100 g), urinary sodium excretion assessed through 24-hour urine samples and blood pressure. Trial process measures will be collected and qualitative assessment will provide insights into participant engagement with the intervention content and perceived barriers to and facilitators of salt reduction dietary behavioural change.

**Discussion:**

If the outcomes indicate the trial is feasible and there is evidence that behavioural change may result in salt reduction, we will proceed to a definitive trial to test the effectiveness of the intervention to lower blood pressure. If successful, this intervention approach could be applied not only to people with high blood pressure, but also to the wider population with normal blood pressure in whom dietary salt intake exceeds recommendations.

**Trial registration:**

ISRCTN, 20910962. Registered on 5 April 2017.

## Background

Cardiovascular disease (CVD) is the leading cause of premature mortality globally and a significant contributor to preventable morbidity [1–4]. Hypertension is one of the most significant risk factors for CVD, and a key contributor to the global burden of disease [5, 6]. At least one quarter of adults in the UK (and more than half of those older than 60 years) have hypertension [7]. There is a positive association between blood pressure and dietary salt intake [8], both in individuals with hypertension and also in those with normal blood pressure [9]. Despite UK government recommendations for adults to reduce dietary salt intake to < 6 g/day, intake remains high at an average of 8.1 g/day [10], with around three quarters of this derived from packaged or processed foods [11]. Overall, 70% of the adult population are estimated to have salt intake > 6 g/day [10].

Clinical trials have proven that dietary interventions with intensive support to reduce salt intake, sometimes involving the provision of low-salt foods, can significantly reduce systolic blood pressure, by up to 7 mmHg [12–14]. In addition, systematic reviews have demonstrated that advice-based interventions such as nutritional counselling or tailored education can be effective [15, 16], but the effectiveness of these interventions depends largely on intensity. Interventions most likely to be effective are those including moderate-to-high-intensity advice, involving multiple one-to-one or group counselling sessions [17]. The challenge is that such interventions are not feasible to deliver at scale by non-specialist staff without a significant expansion in the workforce and training. At present any dietary advice in routine primary care usually consists of non-tailored information to help patients maintain a low-salt diet [7]. There is a wide range of salt content in foods within and between product categories, and it is difficult for non-specialists to provide accurate and personalised advice to help individuals achieve a low-salt diet.

Brief behavioural interventions have been used successfully in primary care to encourage smoking cessation [18] and reductions in alcohol intake [19] but evidence on the effectiveness of brief interventions for dietary change is limited. A recent pilot study of a low-intensity dietary counselling intervention to reduce blood cholesterol demonstrated a significant beneficial short-term effect [20], indicating potential for a brief-intervention approach. However, a study of a brief intervention to reduce blood pressure, covering a range of strategies including diet, showed no effect [21], and there is currently no established brief intervention known to be effective to reduce salt intake.

One approach to magnify the effectiveness of advice-based interventions for dietary change is to use technology to deliver personalised advice at the point at which individuals make a choice about the food and drink they buy or consume. Studies using digital tools such as smartphone applications (apps) as a standalone intervention to reduce salt intake indicate their potential effectiveness [22, 23].

This study investigates the feasibility of a trial examining a complex, behaviour change intervention to reduce salt intake, combining brief advice delivered by non-specialist health practitioners in primary care with use of an app to guide food-purchasing decisions. It aims to motivate and support individuals with high blood pressure to reduce their salt intake by swapping to lower-salt products when grocery shopping. A definitive trial to show whether this intervention is effective at lowering salt intake and blood pressure would need to be large and would be expensive. Before this is justified, we need to ensure that people engage with the intervention, that it can reduce salt intake in the short term and that the research methods run as expected.

## Objectives

The primary aim of this study is to test the feasibility of a randomised controlled trial (RCT) to study the effectiveness of this complex behavioural intervention to lower salt intake in people with raised blood pressure. The primary objectives are therefore to assess the criteria for progression to a full trial, which would examine the effect on blood pressure. The primary objectives will assess the:
Rate of attendance at the follow-up sessionProportion of the essential intervention elements that are delivered in the intervention sessionProportion of participants using the Salt Swap app

Secondary objectives are to:
Gain an indication of effectiveness of the intervention in terms of salt intake, salt content of purchased foods and blood pressure at follow-upUnderstand the barriers and facilitators of successful engagement with the intervention

We will also test the trial procedures through a range of process measures.

## Methods

### Trial design and setting

This trial will be an individually randomised, parallel, two-arm, controlled feasibility trial with a 2:1 (intervention to control) allocation ratio. The primary outcome will be the criteria to progress to a full trial. Process evaluation and analysis of effectiveness outcomes may inform a future trial. Participants will be recruited through five primary care practices in Oxfordshire, UK.

### Recruitment

Practices will search the electronic health records of registered patients to find people who meet the age and blood pressure inclusion criteria. Prior to sending out the invitation letters, the general practitioner (GP) will screen the search results to ensure that all those identified are medically appropriate to participate in the trial and meet the clinical inclusion criteria. The practice will send potential participants an invitation letter asking them to contact the research team if they are interested in participating; the letter will also include a link to an electronic version of the participant information sheet. GPs may also identify eligible patients opportunistically during routine consultations or via the National Health Service (NHS) Health Check programme. We will aim to randomise 40 participants in the study.

### Eligibility criteria

#### Inclusion criteria

The inclusion criteria are:
Most recent systolic blood pressure reading in the past 2 years > 130 mmHg if they are currently taking anti-hypertensive medication or > 140 mmHg if non-medicatedIf on pharmacological treatment for hypertension, the participant has been prescribed a stable dose for at least 6 weeksWilling and able to give informed consent for participation in the studyMale or female, aged between 18 and 80 yearsEnglish speakingRegularly shop in a supermarket (excluding online supermarkets), spending at least £25 at least once a fortnightOwn a smartphone (android or iOS) and prepared to use an app for healthy eatingExpress a desire for support to improve the nutritional quality of their diet to reduce their CVD risk

#### Exclusion criteria

The exclusion criteria are:
Currently on a clinician-supervised diet or a restricted dietCurrently using or have experience of using the Foodswitch or Saltswitch appsUnable to read and understand the instructions provided in EnglishHave secondary, previous accelerated or malignant hypertension documented in the electronic patient recordCurrently being assessed for diagnosis of hypertensionCurrently on any medication that may lead to hyponatraemia or fluid retentionExisting or recent cardiovascular conditions: heart attack or stroke within the last 3 months, heart failure of New York Heart Association grade II and more severe or prolonged QT syndrome, angina, arrhythmia or atrial fibrillationCurrently participating in another research studyConsidered by the GP as not suitable for or unable to meet the demands of the study or unlikely to comply with study procedures as stated in the protocolPlanning to be away from home for more than 2 weeks consecutively during the 6-week intervention period

### Intervention and comparator

#### Intervention

This study investigates the Salt Swap intervention, which aims to help people swap to lower-salt alternatives for everyday foods when grocery shopping. The intervention development was informed by two established behaviour change frameworks, the Behaviour Change Wheel [24] and the Theoretical Domains Framework (TDF) [25]. These theoretical frameworks were used to identify the key determinants of behaviour, particularly the aspects of capability, opportunity and motivation, that need to be influenced in order to support people to reduce purchases of high-salt foods and drinks. The intervention development is described elsewhere.

The intervention incorporates motivation and education, problem solving, goal setting and action planning. It comprises two main components: brief advice provided by a healthcare professional (HCP) at the GP practice and instructions to use the Salt Swap app. Healthcare professionals, typically practice nurses or healthcare assistants, will be trained by one face-to-face training session with a researcher and by video-based training materials. The content of the 20-min one-to-one advice session is based on best practice guidance and information by expert sources including NHS Choices and the British Heart Foundation (BHF) [26, 27]. It is supported by the Salt Swap booklet given to participants during the intervention visit.

This advice incorporates information on:
The impact of salt on health and blood pressure in particularThe health benefits of salt reductionRecommended salt intakeAdvice for cutting salt intakeExamples of lower-salt alternativesSalt reduction goal settingSelf-assessmentAction planning to reduce salt intake

In addition, during this session participants are encouraged to download a novel mobile phone app, Salt Swap, which delivers tailored, salient information on the salt content of products. Users scan a product barcode to receive nutritional information, presented using the traffic light labelling system recommend for use in the UK [28], and are shown suggested lower-salt alternatives. The app contains a database of food and drinks available in UK supermarkets and their nutritional composition. The app allows users to set goals for salt reduction and to receive feedback on the achievement of these goals and the salt reduction achieved through swapping to lower-salt products (see Fig. 1). All other clinical care will continue as usual.

**Fig. 1 Fig1:**
[figure not shown]
Salt Swap app

#### Control (usual care)

Participants randomised to the control arm will receive a copy of the publicly available BHF *Cut Down on Salt* booklet [27] by post, or any revised version of this publication. On completion of their follow-up visit, i.e. when they have completed their participation in the study, they will be sent the same written advice that is given to intervention participants. All other clinical care will continue as usual.

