#### Follow-up

All participants will be invited to attend one follow-up assessment 6 weeks after they receive their allocated intervention (either the intervention visit or the control information sent by post). During this visit, a researcher will measure blood pressure and document any changes to relevant medical history or medications. Participants will be asked to complete an investigator-designed questionnaire to assess aspects of the intervention (or control leaflet) they received.

The follow-up questionnaire will collect data on changes in knowledge about dietary salt intake, awareness of salt intake and dietary-salt-related behaviours. Separate questions for each group will assess how helpful the Salt Swap intervention (advice session and Salt Swap app) or control leaflet were (1–5 scale from very unhelpful to very helpful) as well as the specific reasons why it was considered helpful or unhelpful (for the Salt Swap intervention only). The intervention group questionnaire will also collect data on app acceptability (“would you be interested in using a free app like the Salt Swap app if it was publically available in future?”) and frequency of use (always, most of the time, occasionally, never). Both groups will be asked if any other forms of support (e.g. apps, tools, advice or contact with health professionals) were used throughout the study.

Participants will be asked to submit their grocery shopping receipts for the past 6 weeks and to provide a second 24-hour urine sample at this appointment or within a week of their follow-up visit. The research team will be responsible for arranging follow-up visits. Participants will be contacted by phone in the first instance (unless an alternative contact method is requested by the participant). The research team will use text messages to remind participants of their upcoming appointments.

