#### Secondary outcomes (effectiveness)

The secondary outcomes will be:
Change in salt content of food purchases in the shopping basket, measured as salt in grams per 100 g (and in grams per megajoule) in the intervention compared to the control group; assessed throughout the study through collection of the nutrient composition of all purchased products.Change in salt intake measured through urinary sodium analysis in the intervention compared to the control group; assessed using 24-h urine collection during the baseline period and at the end of the 6-week follow-up appointment. Sodium excretion, reported as millimoles per litre, millimoles per 24 h and total volume of the urine sample, will be converted to daily salt intake in grams using the equation: 17.1 mmol of sodium = 1 g salt, and assumes all of the sodium was derived from salt.Change in blood pressure (systolic and diastolic) in the intervention compared to the control group; recorded at baseline and at the 6-week follow-up.

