#### Process measures

The process measures will be:
Recruitment rates: total recruited and number per practice per month, (including the number invited who were eligible and consented, and the number of recruited participants that completed all baseline assessments and were randomised).Acceptability of the intervention delivery. The perspective of the healthcare professionals responsible for delivering the intervention will be captured via interviews, exploring barriers to and facilitators of delivery and their confidence and belief in their capability to deliver the intervention session.App use and acceptability; measured quantitatively through within-app automatic recording (e.g. frequency of use, number of products scanned per user, frequency of swaps presented and accepted, use of specific behaviour change functionality such as goal setting), and measured qualitatively through the post-intervention survey and think-aloud accompanied shopping trips.Feasibility of data collection: willingness of participants to submit 24-hour urine samples and completeness of shopping data (including completeness of data on the salt content of purchased foods).Evidence of contamination; measured as use of the Salt Swap app by the control group.Changes in participant knowledge, perceptions and behaviours in relation to salt intake and health, measured qualitatively through participant questionnaires and semi-structured interviews.

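### Controls can be sent the intervention's written advice before their follow-up urine is collected, which can bias the secondary urinary-sodium difference toward no effect

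*Protocol article*

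**What the plan says.** Four parts of the protocol article bear on the timing.

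- **Control (usual care)** sets the trigger for releasing the intervention's written material to controls: "On completion of their follow-up visit, i.e. when they have completed their participation in the study, they will be sent the same written advice".
- **Follow-up** places the single follow-up visit 6 weeks after each participant receives the allocated intervention or leaflet. It asks participants "to provide a second 24-hour urine sample at this appointment or within a week of their follow-up visit".
- **Table 1** lists urine collection under Visit 4 with an allowance of up to 7 further days.
- **Secondary outcomes (effectiveness)** defines the urine measure as "assessed using 24-h urine collection during the baseline period and at the end of the 6-week follow-up appointment", and mentions no window after the visit.

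The outcome concerned is "Change in salt intake measured through urinary sodium analysis in the intervention compared to the control group". In the intervention arm, the written material is a booklet that accompanies the advice session: "It is supported by the Salt Swap booklet given to participants during the intervention visit". The Process measures section has one contamination item: "Evidence of contamination; measured as use of the Salt Swap app by the control group".

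**The concern.** The trigger treats the end of the visit as the end of participation, but a control may still owe an outcome sample at that point. If the advice is posted straight away, that control can receive it before or during the urine collection. Only controls get new material at this stage, so any dietary response lowers sodium excretion in that arm alone and shrinks the estimated difference.

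Urinary sodium is the trial's only measure of salt intake. The Background says the team needs to know that the intervention can reduce salt intake in the short term before a definitive trial is justified, and the Discussion intends the data to inform later power calculations. A diluted estimate could make the intervention look weaker than it is.

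The planned contamination measure would not show the problem, because it counts app use only. The questionnaire item on other support is completed at the follow-up visit, before the advice goes out.

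**Working it through.** The article gives no figure for this bias, so there is none to reproduce. The check has two parts: the timing, and what a given exposure would do to the estimate.

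**1. Timing**

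| Event | Day relative to follow-up visit | Source |
|---|---|---|
| Blood pressure, questionnaire | 0 | Follow-up; Table 1 |
| Receipts for the preceding 6 weeks | requested at day 0, covering time before it | Follow-up |
| Advice sent to controls | on completion of the visit | Control (usual care) |
| Second 24-hour urine | 0 to 7 | Follow-up; Table 1 |
| Second 24-hour urine | at the appointment, no window | Secondary outcomes (effectiveness) |

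Read literally, the advice can precede the urine by 0 to 7 days, less delivery time. Blood pressure is taken before dispatch and the receipts cover the period before it. The three progression criteria (attendance, fidelity of delivery, app use) do not depend on the urine sample.

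**2. Effect on the estimate**

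Let D be the true between-arm difference in sodium change, f the share of analysed controls whose urine is collected after the advice reaches them, and r their response as a fraction of D. The control mean moves by f × r × D toward the intervention mean, so the expected estimate is D × (1 − f × r) and the attenuation is f × r. The article gives neither f nor r. The values below are assumptions.

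| f | r = 0.1 | r = 0.5 |
|---|---|---|
| 0 | 0% | 0% |
| 0.25 | 2.5% | 12.5% |
| 0.5 | 5% | 25% |
| 1.0 | 10% | 50% |

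The bottom-right cell needs every control to collect late and also to respond half as strongly as the full intervention. It marks a corner of the grid and is not an expectation.

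**3. How few controls it takes**

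With 40 randomised 2:1, controls number 40/3 ≈ 13. At the 80% follow-up that the Sample size section anticipates, 13.3 × 0.8 ≈ 11 remain. One late collector is then 1/11 ≈ 9% of the control mean. That participant alone attenuates the difference by 0.09 × 0.1 ≈ 0.9% if r = 0.1, or 0.09 × 0.5 ≈ 4.5% if r = 0.5.

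**4. Against the sampling error**

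The intervention arm has 26.7 × 0.8 ≈ 21 analysed. The 95% half-width for a difference in means is 1.96 × √(1/21 + 1/11) ≈ 0.73 SD. For an assumed effect of 0.5 SD, a 25% attenuation is 0.125 SD, well inside that half-width.

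**The case against.** The strongest defence is that the sentence carries its own safeguard. It explains the trigger as the point at which participation is complete, and someone who still owes a urine sample has not completed participation. Table 1 files the urine under Visit 4, so completing the visit could be read to include the sample. That shows the intent. It does not settle the practice, because the sentence as written equates the end of the visit with the end of participation, and the Follow-up section separates the urine from the visit by up to a week. Staff who follow the Control section literally would post the advice while the window is open.

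Three further points stand and limit the size:

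- Exposure needs several things together. The control must not bring the sample to the appointment, and the advice must be posted at once, arrive, be read and change diet before the collection. The share affected may be zero.
- Controls receive only the written material, without the healthcare professional's session or the instruction to use the app, which are the two main components. They have already held the British Heart Foundation salt booklet for 6 weeks, and the session content draws on that same source. The Background says that the effect of advice depends largely on intensity.
- The outcome is secondary, and the article states that the trial is not powered for effectiveness. Any bias is toward no effect, so it cannot create a false sign of benefit.

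A reader might still infer that the salt-intake comparison is contaminated outright, or that most of the effect could be lost: f = 0.75 with r = 1 would give 75%. The article does not support either reading. It makes exposure possible without making it certain, and r = 1 would mean that a second piece of written advice, within days, matches the whole intervention over 6 weeks.

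**Conclusion.** The conflict in the text is clear: the trigger for sending the advice precedes the close of the urine window. The consequence is a possible bias toward no effect in the secondary urinary-sodium difference, confined to controls who collect after the advice reaches them. Its size cannot be derived from the article and is probably modest. It is nil if no control is exposed, 2.5–10% if the response is a tenth of the intervention effect and a quarter to all of the controls are exposed, and 25% if half are exposed and respond half as strongly. All the non-zero figures rest on assumed f and r.

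The point is minor to moderate. It does not threaten the decision rules for progression and is small beside the sampling error of the estimate. It still merits correction, because its direction is known, it is avoidable at almost no cost, and the planned contamination measure would miss it.

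**What to change.** In Control (usual care), change the trigger so that a control is sent the written advice only after the follow-up urine sample has been received, or after its 7-day window has closed if no sample comes. Drop the wording that equates the end of the visit with the end of participation. State the same urine window in Follow-up, Table 1 and Secondary outcomes (effectiveness); the last of these currently gives none.

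Record the date the advice is sent and the date of each follow-up urine collection. Any control exposed under the present wording can then be identified. There is no need to hold the advice for the receipts, since these cover the 6 weeks before the visit.

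The cost is a small edit in each of these places and two dates per control. The only downside for participants is that controls receive the booklet up to about a week later.
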